#### Individualized strength training program

The exercise training program provided by the COPD app consists of a variety of whole-body exercises that will be performed on a daily basis for approximately 15–20 min. Simple sit-to-stand exercises to train large muscle groups in various forms and trunk and upper body resistance exercises that will be performed without supplemental equipment are major components of the training program. Daily strength training always begins with a whole-body warm-up and finishes with two to three appropriate stretching exercises. During the program, the intensity of exercises will progressively increase. All exercises will be explained in exercise videos, which include detailed instructions to ensure the correct performance, training amount, and training intensity. To document the training progress, the patients will record their completed training sessions in the COPD app, which will also be used to monitor training adherence by health care professionals.

#### Exercise concept

The general principle of physical exercise in the physiotherapeutic section of the app is to promote exercise with a focus on strength over endurance training. The exercises are chosen to affect several body parts at the same time. Exercise duration and intensity will initially be chosen depending on the user’s exercise capacity as assessed in the self-test in the app. Using constant reassessment, exercise intensity can be adapted after each day of use of the app. Overall, there are 47 exercises, mostly focusing on strengthening major muscle groups. Exercises vary from easy sitting exercises, for users with a high level of impairment, to standing or lying exercises. All exercises can be performed using a simple training mat, a chair, or sometimes a 1-l bottle of water, without the need for other items. Furthermore, the app promotes overall physical activity in terms of walking. The number of steps each day is collected by the wearable device and reported to the app, and goals for activity will be set weekly depending on the recent individual fitness level. Users are reminded of their activity goals via push notifications in the app.

The COPD app will be used by participants throughout the entire interventional period of 24 weeks.

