**Methods:**

This is the protocol for a randomized, controlled, open-label, multicentered trial that will be carried out at inpatient PR hospital centers in Germany and Switzerland. The interventions will involve the use of the KAIA COPD app program (Arm 1) or an active comparator, i.e., usual care (Arm 2). Patients completing an in-hospital PR program and consenting to participate in the study will be screened with the inclusion and exclusion criteria and enrolled in the study. After fulfilling the screening requirements, the patients will be randomized into one of the two arms with parallel group assignment in a 1:1 ratio. The training program will be delivered to the participants grouped in Arm 1 via the KAIA COPD app and to participants grouped in Arm 2 via the regular recommendations or standard of care by the PI. In total, 104 participants will be included in the trial. The treatment period will last for 24 weeks. Electronic versions of questionnaires will be used to collect patient-reported assessments remotely. The primary outcome measure is the change in physical activity of the intervention group in comparison to the control group, measured over 1 week as the mean steps per day with a Polar A 370 activity tracker, from baseline (end of PR) to the 6-month follow-up. The secondary outcome measures are functional exercise capacity, health status, sleep quality, exacerbation rate, and depression and anxiety symptoms assessed at several intervals.

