### Eligibility criteria {10}

During the recruitment period, all patients with COPD admitted to the PR hospitals will be informed about the ongoing study. Patients who are interested in study participation will receive oral and written information about the study before signing the informed consent for. After signing the informed consent form, participants will be instructed on how to use the activity tracker (Polar A 370) by the local study personnel. Participants will be instructed to wear the activity tracker every day for at least 20 h per day. After the screening period (approximately 8–10 days), eligibility will be judged by the local investigators based on the randomization criteria. If the screening requirements are fulfilled and the participants are deemed eligible, they will be randomized.

Every 2 weeks, an e-link leading to the questionnaires will be sent via email regarding exacerbations (questionnaire defined by the GOLD Guidelines), safety (adverse events or severe adverse events), device deficiencies, and patient feelings. There will be no prohibited medications during the study, and any change in concomitant medications will be noted down biweekly. In addition, at baseline and after 3 and 6 months, another e-link will be sent via email to all participants to complete the CRQ and HADS, to provide instructions to perform the 1-min sit-to-stand test and COPD Assessment Test (CAT), and to evaluate whether participants met their personal goal of physical activity.

Daily steps, sleep efficacy, and total sleep time will be passively collected by a Polar A 370 watch and will be imported to the study-specific electronic case report form (eCRF) system over the Google Fit Server. Figure 1 provides an overview of the study procedures.

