#### Assessment of explanatory outcomes

Explanatory outcomes are patient compliance with the training and the health professionals’ feedback. The satisfaction with the COPD app will be examined with 2 questions (English version, originally in German):
How satisfied are you with the course of your therapy after using the COPD app?
Very satisfiedSatisfiedNot satisfiedWould you recommend the KAIA COPD app to other patients?
YesNo

Achievement of individual goals will be assessed by the participant himself with a questionnaire during a phone call.

Patient compliance and adherence to the training will be assessed every week by the study nurse, who will check the downloaded and viewed training videos (intervention group) and the daily activity, as captured by the activity tracker, of the participants (both groups). In addition, compliance will be assessed by the number of successfully conducted telephone calls (which will be reported by the health professionals who conduct the interventions).

Satisfaction and experience with the COPD app will be assessed by a satisfaction questionnaire at the 6-month follow-up visit (intervention group only).

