### Implementation {16c}

Randomization will be performed on the patient level with a 1:1 ratio using block randomization with varying block sizes, stratified per study center. Once the random number is delivered to the study site, it is the duty of the site personal to implement the procedures as specified in the protocol.

The study nurse will carry out a short training program (20 min) to demonstrate the use of the wearable and mobile device platform (smartphone) for both groups. Additionally, the following steps will be taken to explain the group assignment to the subjects.

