#### Control group

Setting the individual goals for physical activity (steps per day)Synchronization of the smartphone

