### Assignment of interventions: open label study

#### Who will be blinded {17a}

Patients cannot be blinded due to the nature of the intervention. Blinding of statisticians or data managers will be carried out.

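### Attainment of the personal activity goal may not be comparable between arms: the goal is set after allocation, patients rate it themselves, and the plan does not say which goal is meant

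*Protocol article*

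**What the plan says.** All places are in the protocol article.

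- **The item.** Under Eligibility criteria {10}, an e-link goes to all participants at baseline, 3 and 6 months, among other things "to evaluate whether participants met their personal goal of physical activity". Under Assessment of explanatory outcomes: "Achievement of individual goals will be assessed by the participant himself with a questionnaire during a phone call".
- **The goal set at assignment.** Implementation {16c} describes what happens once the random number has reached the site: "the following steps will be taken to explain the group assignment to the subjects". The lists for the intervention group and the control group then contain the same step: "Setting the individual goals for physical activity (steps per day".
- **The weekly goals.** Exercise concept says of the app that "goals for activity will be set weekly depending on the recent individual fitness level", and that "Users are reminded of their activity goals via push notifications in the app". According to Explanation for the choice of comparators {6b}, controls cannot open the app's content.
- **Blinding.** Who will be blinded {17a}: "Patients cannot be blinded due to the nature of the intervention".
- **The primary outcome.** The abstract defines it as physical activity "measured over 1 week as the mean steps per day with a Polar A 370 activity tracker". It does not refer to any goal.

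**The concern.** A yes/no answer on goal attainment means the same in two arms only if the goal is set in the same way in both and the answer is obtained in the same way. Three features put that in doubt.

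1. The goal is agreed while the group assignment is being explained. Patient and staff both know the arm, so how ambitious the goal is can depend on the arm.
2. The rater is the unblinded patient, although the watch records the steps that would settle the question.
3. App patients receive further goals every week, with reminders, and the question does not say which goal it means.

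At stake is the reading of this one item. A higher attainment rate in the app arm could reflect an easier or a moving goal and not more walking. That would matter if the item were cited as support for maintenance of activity after rehabilitation.

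**Working it through.** The documents give no figure for goal attainment, so there is none to reproduce. The check sets the passages side by side and then tests by calculation whether the mechanism could matter.

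**Step 1. Compare the arms.**

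| Feature | App arm | Control arm |
|---|---|---|
| Individual step goal at the assignment session | yes | yes, same wording |
| Allocation known when that goal is set | yes | yes |
| Weekly goals with reminders | yes (Exercise concept) | none described; no access to app content |
| Who rates attainment | unblinded patient | unblinded patient |
| Goal the question refers to | not stated | not stated |

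The second and fourth rows are the same in both arms. They open the way to bias but do not by themselves create an arm difference. The third row differs by arm, and it matters only if the last row is resolved in favour of the weekly goal.

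**Step 2. Could a weekly goal change the answer?** All inputs are assumptions: 5000 steps/day at the start; weekly means vary with a coefficient of variation of 15%; steps fall by a fraction r per week for 24 weeks; the goal is g times the observed mean of a reference week, with g from 0.95 to 1.05. The reference week is week 23 for a reset goal and week 0 for a fixed goal. With normal variation, the probability that week 24 meets the goal is

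Φ[(μ24 − g·μref) / (0.15·√(μ24² + g²·μref²))], where μt = 5000·(1 − r)^t.

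Example with r = 1% and g = 1: μ24 = 3928 and μ23 = 3968.

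- Reset goal: (3928 − 3968) / (0.15·√(3928² + 3968²)) = −40/838 = −0.05, so about 48%.
- Fixed goal: (3928 − 5000) / (0.15·√(3928² + 5000²)) = −1072/954 = −1.12, so about 13%.

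A simulation with 200,000 draws per cell gives, from g = 1.05 to g = 0.95:

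| Weekly fall | Steps at week 24 | Goal reset weekly | Goal fixed at start |
|---|---|---|---|
| 0% | 5000 | 41–60% | 41–60% |
| 1% | 3928 | 39–58% | 9–19% |
| 2% | 3079 | 37–56% | 1–3% |

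With stable activity the two kinds of goal agree. With falling activity they separate widely although the steps are identical.

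**Step 3. Could goal difficulty alone change the answer?** Take the first row, where activity is unchanged and the goal is fixed. A goal 5% below the baseline week is met by about 60%, and a goal 5% above it by about 41%. If goals set with the allocation known differed by that much between arms, attainment would differ by about 19 percentage points with no difference in steps. Whether goals would differ by arm, and by how much, the documents cannot say.

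**Step 4. Mode of collection.** Eligibility criteria {10} describes an e-link; Assessment of explanatory outcomes describes a phone call. The regular calls in Intervention description {11a} concern the app's exercise programme, so the mode could differ by arm, though the text does not say that it does. The item is also asked at baseline, while no goal is described before the assignment session.

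**The case against.** The strongest reply is that the text points to a common reference. Assessment of explanatory outcomes speaks of individual goals, which is the term used for the step in both assignment lists. Exercise concept presents the weekly goals as a feature of the app. On that reading both arms answer about a goal set in the same way, and the gap in Step 2 does not arise. The article also plans no comparison of attainment between arms, leaves the detail of the explanatory analyses to a separate statistical analysis plan, and tests its main objective on tracker steps. Asking patients whether they met a personal goal is a legitimate patient-reported item.

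Much of this stands, and it rules out stronger readings that a reader might infer:

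- *That attainment is judged against the weekly app goals by design.* No section says so.
- *That controls receive one goal only.* No update is described for them and the app is closed to them, but no section excludes an update.
- *That the app goal follows a declining patient downwards.* Exercise concept ties the goal to recent fitness and gives no rule. This outcome is possible but not stated.
- *That identical activity must give opposite answers.* It need not. Suppose two patients fall smoothly from 6000 by 300 steps every 4 weeks (75 per week), to 6000 − 6 × 300 = 4200 at week 24. The control misses a fixed goal of 6000 by 1800 (30%). The app patient, with a goal reset to the previous week's 4275, misses by 75 (about 2%). Both would truthfully answer no. The gap in Step 2 needs week-to-week variation.

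The reply does not remove the order of events or the rater. An analysis plan written later cannot undo goals agreed with the allocation known, nor recover which goal a patient had in mind. These are matters of conduct, and this document fixes the first and leaves the second open.

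**Conclusion.** The point holds in limited form. Attainment of the personal activity goal may not be comparable between arms, because the goal is set after allocation, unblinded patients rate it, and the reference goal is not named while only the app arm has goals that change weekly.

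The size is conditional. If patients answer about the weekly goal and activity falls by 1% a week, attainment would be 39–58% against 9–19% for the same steps, on assumed inputs. If the goal set at assignment is the reference in both arms, this asymmetry is zero and only the setting after allocation and the self-rating remain. Neither of those has an effect that can be estimated from the documents.

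The weight is low. The item is explanatory, no efficacy claim is attached to it, and the primary step outcome does not depend on any goal.

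**What to change.** 1. Set the individual step goal by the same rule in both arms before the sponsor releases the allocation e-mail described in Concealment mechanism {16b}.
2. For any comparison between arms, score attainment at 3 and 6 months from tracker steps, against that fixed goal or the patient's own baseline mean.
3. State in the question which goal is meant, and keep the patient's own rating as descriptive information only.
4. Report attainment of the weekly app goals within the app arm only, as a measure of use.
5. Reconcile the e-link with the phone call as the mode of collection, with the same mode in both arms, and say what the baseline question refers to.

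The cost is a small change in the order of the assignment session, one variable derived from step data already collected, and some clarifying text. No visit or instrument is added.

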#### Criteria for discontinuing or modifying allocated interventions {11b}

Each participant will be informed that participation in the study is voluntary, that he/she may withdraw from the study at any time, and that withdrawal of consent will not affect his/her subsequent medical assistance and treatment. The study might be prematurely terminated due to ethical concerns or insufficient participant recruitment or when the safety of the participants is doubtful or at risk, when alterations in accepted clinical practice make the continuation of a clinical trial unwise or when there is early evidence of benefit or harm of the experimental intervention.

For participants who prematurely stop the study, follow-up assessments that are normally conducted during visits 5 and 8 will be conducted at the point of termination only if the participants agree.

#### Strategies to improve adherence to the interventions {11c}

There will not be any additional strategies to improve adherence to the intervention.

#### Relevant concomitant care permitted or prohibited during the trial {11d}

Concomitant care will be allowed to continue during the study period.

### Provisions for posttrial care {30}

Provisions, if any, for ancillary and posttrial care and for compensation to those who suffer harm from trial participation will be provided.

### Outcomes {12}

During the study, no in-person visits will be planned for the study participants, and the assessments will be performed using electronic patient-reported outcomes (ePRO) by sending links to the participants. They will perform all required assessments by themselves, and the results will be directly transferred to the eCRF. The results of the assessments will be checked regularly by the study personnel of the site where the participants were recruited.

Daily steps, sleep efficacy and total sleep time measured passively and continuously for each participant by the activity tracker during the treatment period will be transferred and saved to the study eCRF database by Google Fit.

#### Assessment of the primary outcome

The primary outcome assessment will be the measurement of physical activity, recorded as steps every day (provided by the activity tracker Polar A 370), for 6 months for the intervention group as well as for the control group. Data regarding the steps per day will be transferred from the Polar watch to the smartphone via Bluetooth. Data from the KAIA COPD app will be sent to the KAIA database server via the internet. Therefore, all participants will be equipped with a smartphone that has internet access at home (the intervention group will also have access to the COPD app) and with a Polar watch (see Fig. 1).

#### Assessment of secondary outcomes

Secondary outcomes will be measured at three time points: during the baseline visit and at the 3- and 6-month follow-up visits/early termination visits via an email link sent by the study staff.

#### Assessment of explanatory outcomes

Explanatory outcomes are patient compliance with the training and the health professionals’ feedback. The satisfaction with the COPD app will be examined with 2 questions (English version, originally in German):
How satisfied are you with the course of your therapy after using the COPD app?
Very satisfiedSatisfiedNot satisfiedWould you recommend the KAIA COPD app to other patients?
YesNo

Achievement of individual goals will be assessed by the participant himself with a questionnaire during a phone call.

Patient compliance and adherence to the training will be assessed every week by the study nurse, who will check the downloaded and viewed training videos (intervention group) and the daily activity, as captured by the activity tracker, of the participants (both groups). In addition, compliance will be assessed by the number of successfully conducted telephone calls (which will be reported by the health professionals who conduct the interventions).

Satisfaction and experience with the COPD app will be assessed by a satisfaction questionnaire at the 6-month follow-up visit (intervention group only).

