#### Intervention description {11a}

The study intervention consists of training sessions conducted daily by the patient via the COPD app. Regular contacts via telephone calls will be conducted by the same health care professional with respect to the realization and execution of the exercise training program shown in the COPD app. Patients will be contacted by phone if they do not meet the exercise criteria (exercising with the app at least 4 out of 7 days a week).

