#### Per-protocol analysis

As a sensitivity analysis, we will additionally conduct a per-protocol analysis, where we will also compare the control group with the intervention group but where we will only retain those participants in the intervention group who adhered to the intervention for the analyses.

We define adherence to the protocol (in terms of exercise training) as conducting the exercise training sessions for at least 70% of the weeks the patients are able to train (i.e., weeks when patients suffered from exacerbations or other health conditions that prevent them from training will not be considered; as discussed with the coach), for at least 4 times a week, during the 6 months of the intervention (see the following definitions):
Definition of a fulfilled individualized training session per day (according to the protocol: 3 different exercises per day are scheduled): completion of at least 2 different exercises per dayDefinition of a fulfilled week of training (rate of training sessions according to the protocol: 4 per week): completion of at least 4 out of the planned 7 individualized training sessions per week on average.

We will adjust the per-protocol analyses with prognostic factors for the primary outcome steps per day, lung function (FEV1), exercise capacity and exacerbation events, for adherence to conduction of the exercises (self-efficacy to conduct the exercises, exercise capacity, dyspnea, and acute worsening of health state [exacerbations and other]) and for whether the patients conducted other exercise strength training.

Concerning the control group, we will collect as much information as possible, especially with respect to the type and frequency of self-organized exercise training. This will also be included in the per-protocol analysis.

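### The supplementary count of completed telephone calls can rise when training is missed, so as written it cannot be read as compliance

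*Protocol article*

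**What the plan says.** Two sections of the protocol article bear on this.

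- **Intervention description {11a}** gives two reasons for phoning a patient. The first is routine: "Regular contacts via telephone calls will be conducted by the same health care professional". The second depends on behaviour: "Patients will be contacted by phone if they do not meet the exercise criteria", the criterion being use of the app for exercise on at least 4 of 7 days. No number or interval is given for the routine calls.
- **Assessment of explanatory outcomes** sets the status of the measure: "Explanatory outcomes are patient compliance with the training and the health professionals’ feedback". Each week the study nurse "will check the downloaded and viewed training videos (intervention group) and the daily activity, as captured by the activity tracker". As an addition to those checks, "compliance will be assessed by the number of successfully conducted telephone calls", and these calls are ones "which will be reported by the health professionals who conduct the interventions". No denominator is stated, and routine calls are not separated from calls prompted by missed training.

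The **Per-protocol analysis** section defines adherence without reference to calls: "conducting the exercise training sessions for at least 70% of the weeks the patients are able to train", with at least 4 sessions a week.

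**The concern.** A compliance measure should move in one known direction as compliance improves. Here one of the two sources of calls is set off by non-compliance. A patient who falls short of the training criterion more often is due more phone contact and, if the phone is answered, collects a higher count. A patient who always trains is due only the routine calls. The count therefore mixes willingness to take planned calls, which is a reasonable sign of engagement, with the number of prompts received, which is a sign of the opposite.

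What is at stake is how one descriptive measure is read. The Objectives section sets out to explore compliance and adherence and to identify what helps implementation at home. If this count were tabulated or related to other variables for that purpose, it could disagree with the video and tracker data for reasons that come only from its construction.

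**Working it through.** The article gives no figure for this measure, so there is nothing to reproduce. The check sets the two sections side by side and then illustrates the direction of the count.

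**Input from the article**
- The app is used for 24 weeks (Exercise concept).

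**Assumptions (not in the article)**
- *R*, the number of regular calls: 0, 6, 12 or 24.
- *a*, the share of calls answered.
- One triggered call for each week in which the criterion is missed.

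**Formula.** With *m* weeks meeting the criterion,

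expected completed calls = *a* × (*R* + 24 − *m*).

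**Expected counts**

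| *R* | *m* = 24, *a* = 0.95 | *m* = 12, *a* = 0.80 | *m* = 0, *a* = 0.60 | *m* = 0, *a* = 0.10 |
|---|---|---|---|---|
| 0 | 0.0 | 9.6 | 14.4 | 2.4 |
| 6 | 5.7 | 14.4 | 18.0 | 3.0 |
| 12 | 11.4 | 19.2 | 21.6 | 3.6 |
| 24 | 22.8 | 28.8 | 28.8 | 4.8 |

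For example, with *R* = 6 a fully adherent patient has 0.95 × 6 = 5.7 completed calls. A patient who never meets the criterion and answers 60% of calls has 0.60 × 30 = 18.0. If that patient answers only 10%, the count is 0.10 × 30 = 3.0 and the order is restored.

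**Break-even.** The never-adherent patient outscores the fully adherent one when *a* × (*R* + 24) > 0.95 × *R*, that is, when *a* > 0.95 × *R* / (*R* + 24):
- *R* = 0: any answering at all.
- *R* = 6: 5.7 / 30 = 19%.
- *R* = 12: 11.4 / 36 = 32%.
- *R* = 24: 22.8 / 48 = 48%.

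**Simulation across patients.** 200,000 simulated patients were given a weekly probability *p* of meeting the criterion, uniform on 0 to 1, over 24 weeks. Completed calls were Bin(*R*, *a*) + Bin(missed weeks, *a*). The table gives the correlation of the count with weeks meeting the criterion.

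| *R* | *a* = 0.8 for all | *a* = 0.3 + 0.6*p* |
|---|---|---|
| 6 | −0.96 | −0.48 |
| 12 | −0.95 | −0.12 |
| 24 | −0.92 | +0.43 |

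With *R* = 6, patients with at most 6 fulfilled weeks average 21.6 calls when *a* = 0.8 (10.5 when answering depends on adherence). Those with at least 20 fulfilled weeks average 6.4 (6.6).

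The sign is negative in five of these six settings and positive in one. It is set by quantities the article does not state.

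**The case against.** **The count may be meant for regular calls only.** The calls are reported by the professionals who deliver the intervention, and the routine contacts are made by the same professional, so this is a possible reading. On it, the measure would run the right way. The wording does not limit the count in this way, however, and nothing tells those reporting the calls to separate the two kinds.

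**One extra call per missed week is not in the text.** This stands. A missed week might be dealt with inside a routine call, and the study schedule figure is not available to this review. The numbers above are illustrations only.

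**Detail is left to the statistical analysis plan.** The Secondary analyses section defers how the explanatory outcomes are analysed, and a denominator could be set there. But the article does more than leave a gap: it names the quantity to be counted, and that quantity as worded includes calls prompted by non-adherence.

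**The reach is small.** This also stands. A reader might infer that the trial's compliance outcome as a whole would run backwards, or that fully adherent patients will score lowest. The article does not support either. The call count comes on top of video and tracker checks that run the right way, and the order is restored when non-adherent patients seldom answer. Nor does the article describe any dose-response or other model that uses the call count.

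**Conclusion.** The concern holds in a limited form. If all completed calls are counted as written, missed training can raise the figure, and the result cannot be interpreted as compliance. The direction is uncertain rather than reliably reversed: the illustrative correlations run from −0.96 to +0.43. They rest on assumed numbers of regular calls, answering rates, spread of adherence and one triggered call per missed week.

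It would be wrong to infer that the per-protocol or primary result is at risk. Per-protocol adherence is defined by training sessions, and the primary analysis of steps per day does not use call data. Severity is minor: one supplementary measure within an explanatory outcome.

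**What to change.** In Assessment of explanatory outcomes, replace the count with a defined proportion, for example:

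*Call compliance is the number of regular scheduled calls completed divided by the number of regular calls attempted. Calls made because the training criterion was missed are reported separately, as an indicator of non-adherence, and do not enter any compliance measure.*

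Add a call-type field (regular or triggered) to the call log, filled in at the time of the call because later reconstruction is less reliable. If a missed week is discussed during a regular call, log that call as regular.

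The cost is one sentence in the protocol or analysis plan and one field on the log. It needs no additional patients, visits or calls, and it leaves the rule for when patients are phoned as it is.
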